## Abstract

**Introduction:**

South Asians have high rates of cardiovascular disease (CVD) and its risk factors (hypertension, diabetes, dyslipidaemia and central obesity). Left ventricular (LV) hypertrophy and dysfunction are features of these disorders and important predictors of CVD mortality. Lower birth and infant weight and greater childhood weight gain are associated with increased adult CVD mortality, but there are few data on their relationship to LV function. The IndEcho study will examine associations of birth size, growth during infancy, childhood and adolescence and CVD risk factors in young adulthood with midlife cardiac structure and function in South Asian Indians.

**Methods and analysis:**

We propose to study approximately 3000 men and women aged 43–50 years from two birth cohorts established in 1969–1973: the New Delhi Birth Cohort (n=1508) and Vellore Birth Cohort (n=2156). They had serial measurements of weight and height from birth to early adulthood. CVD risk markers (body composition, blood pressure, glucose tolerance and lipids) and lifestyle characteristics (tobacco and alcohol consumption, physical activity, socioeconomic status) were assessed at age ~30 years. Clinical measurements in IndEcho will include anthropometry, blood pressure, biochemistry (glucose, fasting insulin and lipids, urinary albumin/creatinine ratio) and body composition by dual energy X-ray absorptiometry and bioelectrical impedance. Outcomes are LV mass and indices of LV systolic and diastolic function assessed by two-dimensional and Doppler echocardiography, carotid intimal-media thickness and ECG indicators of ischaemia. Regression and conditional growth models, adjusted for potential confounders, will be used to study associations of childhood and young adult exposures with these cardiovascular outcomes.

**Ethics and dissemination:**

The study has been approved by the Health Ministry Steering Committee, Government of India and institutional ethics committees of participating centres in India and the University of Southampton, UK. Results will be disseminated through scientific meetings and peer-reviewed journals.

**Trial registration number:**

ISRCTN13432279; Pre-results.

Strengths and limitations of this studyThe strengths include the longitudinal study design with early growth data, which allows examination of the relationship of size at birth, childhood growth and cardiovascular disease risk markers in young adult life with myocardial structure and function in midlife in South Asians.The two cohorts represent both rural and urban populations, north and south India and diverse socioeconomic strata.The study will use harmonised methods to measure anthropometry, biochemical risk factors and to characterise lifestyle factors.A limitation of the study is attrition of the cohorts due to deaths and migration (mainly in childhood).Because this is a field-based study, echocardiography will be used, rather than cardiac MRI, which is the current gold standard method for measuring myocardial structure.

## Introduction

### Background and rationale

The emerging epidemic of cardiovascular disease (CVD) in transitioning populations means that low/middle-income countries (LMICs) contribute a larger proportion to the global burden of CVD (~8–9 million deaths per year) than high-income countries (~5 million).^1–3^ Migrants from LMICs to high-income countries experience an excess of CVD compared with indigenous populations.^4–6^ A parallel increase in the prevalence of hypertension, type 2 diabetes (T2DM) and obesity, which are known risk factors for CVD is also observed in LMICs.^7 8^

Altered myocardial structure and function have received less attention as causes of cardiac death than ischaemic heart disease (IHD). Left ventricular hypertrophy (LVH) increases the future risk of heart failure and death^9^ through volume overload, pressure overload and myocyte loss.^10 11^ LVH is usually asymptomatic for several years before the development of congestive heart failure. Obesity, hypertension, T2DM and IHD initiate LV remodelling and dysfunction and enhance progression to heart failure.^11 12^ The prospective Coronary Artery Risk Development in (Young) Adults (CARDIA) study showed that higher blood pressure, body mass index (BMI), waist circumference, cholesterol, triglyceride and glucose concentrations at age 18–30 years are risk factors for LV diastolic dysfunction 5–10 years later.^13^ However, these traditional risk factors explain less than half the variability in echocardiographic parameters in population studies.^14 15^

South Asians develop CVD and T2DM, often in combination, a decade earlier than white Caucasians.^16 17^ Several factors contribute to this premature disease: (1) lifestyle changes (the adoption of less healthy diets and reductions in physical activity, consequences of rapid socioeconomic transition), (2) a characteristic pattern of risk factors (low high-density lipoprotein (HDL) cholesterol, elevated lipoprotein (a) and high insulin resistance)^18 19^ and (3) a ‘thin-fat’ body composition (low muscle mass but centrally adipose),^19 20^ the latter two being evident even at birth.^21 22^

South Asian newborns have a low mean birth weight (2.6–2.7 kg) compared with white Caucasian babies^21 23^ and frequently show suboptimal growth and weight gain during infancy.^24^ Low birth and infant weight are risk factors for CVD mortality in adult life and have also been linked to a high risk of hypertension and T2DM.^25 26^ It has been suggested that these associations reflect ‘developmental programming’, permanent structural and functional deficits in key metabolic organs (eg, liver, pancreas and kidneys) and tissues (eg, muscle) resulting from impaired nutrition during fetal and early childhood development.^27^ Studies in India have linked lower birth weight to higher blood pressure, serum lipids and abnormal glucose tolerance in children and adults.^28–30^ The risks associated with lower birth weight appear to be increased on subsequent exposure to greater child or adult weight gain. Upward crossing of BMI centiles in childhood and adolescence is associated with increases in several CVD risk factors such as higher adult cholesterol, triglyceride and proinflammatory marker concentrations and with an increased risk of obesity, impaired glucose tolerance or T2DM (figure 1), hypertension and metabolic syndrome.^29 31^

**Figure 1 F1:**
[figure not shown]
BMI SD scores from birth to adulthood for participants in each cohort who developed IGT or diabetes (n=219/1562 in NDBC and 424/2218 in VBC) in adult life relative to the whole cohort (dashed zero line). BMI, body mass index; IGT, impaired glucose intolerance; NDBC, New Delhi Birth Cohort; VBC, Vellore Birth Cohort.

Early life factors may also influence cardiac structure and function. Growth restricted fetuses and newborns have impaired LV function,^32–34^ thought to be caused by hypoxia, raised placental resistance and altered fetal circulation.^35^ Studies relating birth weight to adolescent or adult LV size, in a variety of populations, have shown a positive association^36^ or a non-significant inverse association.^37 38^ In the latter two studies, low weight in infancy was associated with higher adult LV mass and concentric LVH. Several studies have shown that higher childhood BMI is associated with higher LV mass in childhood and adult life and an increased risk of adult LVH.^36 39 40^

There are few population-based data on the prevalence of echocardiographic abnormalities among South Asians. Indian migrants to the UK present with heart failure younger than white British men and women.^41^ The echocardiographic imaging of healthy individuals in the UK London Life Sciences Prospective Population (LOLIPOP) study showed that South Asians have poorer diastolic function, threefold higher prevalence of LVH and a greater degree of concentric remodelling.^42^ The UK Southall And Brent REvisited Study (SABRE) study showed that the impact of hyperglycaemia on LV mass and function was more adverse in South Asians.^15^ One previous Indian study has investigated LV mass in relation to birth size; it found low mean LV mass compared with white Caucasian populations and an association of longer birth length with higher adult LV mass.^43 44^

Thus, several factors along the life course are related to adult LV hypertrophy and dysfunction, including greater adiposity, longer duration of adiposity, higher blood pressure and lipids, impaired glucose tolerance and early-life growth patterns (figure 2). The current IndEcho study was designed to investigate these relationships in two large population-based Indian birth cohorts.

**Figure 2 F2:**
[figure not shown]
Pathways to altered left ventricular (LV) structure and function that will be investigated in IndEcho. Factors contributing to LV hypertrophy. Intrauterine undernutrition alters the fetal circulation, which may have direct and persistent effects on ventricular structure. Intrauterine and infant undernutrition impairs the development of key metabolic tissues (muscle, pancreas, liver, blood vessels and kidneys) during critical periods of growth and increases adipose tissue deposition, leading to the ‘thin-fat’ phenotype and later obesity, T2DM, dyslipidaemia, hypertension and chronic renal disease, which adversely impact on LV size and function. BMI, body mass index; LV, left ventricular; T2DM, type 2 diabetes mellitus.

### Hypotheses

The prevalence of LVH and LV dysfunction and carotid intimal-media thickness (cIMT) will be positively related to current midlife cardiometabolic risk factors;After adjusting for current cardiometabolic risk factors, LVH, LV dysfunction and cIMT will be positively related to cardiometabolic risk factors measured 12–16 years ago in young adulthood;LVH, LV dysfunction and higher cIMT will be associated with lower birth weight, lower weight in infancy (the first two postnatal years) and faster BMI gain during childhood and adolescence;The associations of LVH, LV dysfunction and cIMT with adult cardiometabolic risk factors will be stronger in men and women who had lower birth or infant weight.

## Methods and analysis

### Study design

Multicentre observational cohort study.

### Study population

The IndEcho study started in November 2016 and will continue until 2019. Participants will be recruited from two Indian birth cohorts: the New Delhi Birth Cohort (NDBC)^29 45^ and Vellore Birth Cohort (VBC).^46^ Both were established in 1969–1973, originally to study maternal health and pregnancy outcomes. The participants were measured at various time points through infancy, childhood, adolescence and early adulthood to assess growth and were subsequently followed up at approximately 30 and 40 years of age to measure a range of CVD risk markers. Flow charts of the different stages of follow-up and various measurements are provided in figure 3. Currently, the participants are aged 43–50 years and new cases of glucose intolerance, T2DM and hypertension are emerging alongside rapid transitions in lifestyle and socioeconomic status (SES). For the IndEcho study, we aim to recruit approximately 3000 individuals from both cohorts combined.

**Figure 3 F3:**
[figure not shown]
Flow chart of various stages of follow-up of the New Delhi and Vellore Birth cohorts and measurements recorded at each stage. BMI, body mass index; DXA, dual energy X-ray absorptiometry; HC, hip circumference; OGTT, oral glucose tolerance test; PA, physical activity; SES, socioeconomic status.

### The NDBC

In 1969–1972, 20 755 married women of reproductive age living in a 12 km^2^ area of South Delhi were recruited (figure 3). The cohort included 8181 singleton live births from 9169 pregnancies among these women. Gestational age was derived from last menstrual period (LMP) dates. The birth weight, length and head circumference of the babies were recorded within 72 hours of birth (n=7119) and thereafter 3 monthly up to the age of 12 months (n=4104) and 6 monthly until the age of 21 years (n=2892). An average 23 sets of measurements were recorded for each individual from birth until 21 years. The first adult study took place in 1998–2002; 2584 (32%) of the original cohort were retraced, of whom 1526 men and women (then aged 28–31 years) participated in a study of CVD risk factors.^29^ Data on their SES, attained education, family history of disease, tobacco and alcohol consumption, diet and physical activity were obtained using standardised questionnaires. Clinical measurements included anthropometry, blood pressure, an ECG and analysis of plasma glucose (during an oral glucose tolerance test), insulin, lipids and proinflammatory markers. In 2008 (at age 34–39 years), the same measurements were repeated in 1100 cohort members and additionally, cIMT and brachial artery endothelial function were measured^47^ and body composition was assessed using dual-energy X-ray absorptiometry (DXA) in a subset. Excluding 18 known deaths (from a total of 1526 who were followed up during 1998–2002), we aim to recruit as many as possible of the 1508 alive NDBC participants.

### The VBC

From 1969–1973, 20 626 women of reproductive age were recruited within defined areas of Vellore town and adjoining rural villages in Tamil Nadu, in South India^48^ (figure 3). The areas of Vellore town were selected to represent different socioeconomic groups. The cohort comprised 10 691 singleton live babies born to the 20 626 women recruited. Weight and length were recorded at birth (n=10 676) and subsequently in infancy (in the first 3 months, n=5753), childhood (6–8 years, n=5541) and adolescence (10–15 years, n=2672). Gestational age was determined from the mother’s LMP dates. Depending on available funding, VBC members had up to 3 measurements in the first 3 months, up to 2 measurements between 6 and 8 years and up to 5 measurements between 10 and 15 years. The first adult follow-up took place in 1998–2002. Cohort members for whom all birth measurements were available (n=4092) were retraced to participate in an adult follow-up during 1998–2002. Of these 2572 were contactable, and 2218 men and women, then aged 26–32 years, consented to participate in the study. CVD risk factors were assessed using a similar protocol to that for NDBC.^49^ Subsequently in 2013–2014, 1080 participants (50.1% urban), aged 41–45 years, took part in a body composition study, in which the same anthropometric and biochemical parameters were recorded along with detailed body composition using DXA. Excluding 62 known deaths (from a total of 2218 who were followed up during 1998–2002), we aim to recruit as many as possible of the 2156 alive VBC members.

The total number of participants in phases 1 and 2 of adult follow-up in the NDBC and VBC and reasons for losses to follow-up are summarised in online supplementary table 1. We will minimise loss to follow-up through the following algorithm until all non-responders are accounted for: telephone calls/postal letters, meetings with neighbours by field workers and contact with local municipality/postal services to track addresses of migrated individuals.

10.1136/bmjopen-2017-019675.supp1Supplementary file 1

### Measurements in the IndEcho study

Measurements will include anthropometry (height, weight, waist and hip circumferences, skinfold thickness), body composition by DXA (Vellore only) and bioelectrical impedance, hand grip strength, blood pressure, biochemical measurements (an oral glucose tolerance test, fasting plasma insulin and lipids and urinary albumin/creatinine ratio, as a measure of microalbuminuria). Details of the methods used for these measurements are given in table 1. Lifestyle factors (tobacco and alcohol consumption, diet, physical activity, occupation and SES) will be reassessed. Standard questionnaires for diet (food frequency questionnaire),^50^ SES (Standard of Living Index),^51–53^ Global Physical Activity Questionnaire,^54 55^ smoking and alcohol consumption^56^ will be used. Details on the key covariates relating to life style are summarised in online supplementary table 2.

**Table 1 T1:** IndEcho study procedures and platforms used

Study-related procedures	Methods/platforms used
Questionnaire assessments	
Diet	FFQ
Physical activity	GPAQ
Socioeconomic status	NFHS Standard of Living Index
Smoking	NFHS-2 Household Questionnaire
Alcohol consumption	NFHS-2 Household Questionnaire
Anthropometry	
Height	Stadiometer
Weight	Digital weighing scales
Waist circumference	Non-stretchable tape
Hip circumference	Non-stretchable tape
Blood pressure	Omron M3
Biochemistry	
Glucose—fasting	Enzymatic method (autoanalyser)
Glucose—120 min	Enzymatic method (autoanalyser)
Insulin—fasting	Vellore: Radiofluorimetric method
Cholesterol	Delhi: Chemiluminescence immunoassay CHOD-PAP Enzymatic colorimetric method
Triglycerides	GPO-PAP Enzymatic colorimetric method
HDL cholesterol	Direct—two-step enzymatic
LDL cholesterol	Direct—enzymatic colorimetric method
Urinary ACR	Jaffe Method
Skinfold thickness	John Bull/Harpenden skinfold calliper
Bioimpedence	Tanita BC-418/Bodystat 2500
Hand grip	JAMAR dynamometer
DXA	Hologic Discovery
ECG	
Echocardiography	Philips CX50 Compact Xtreme system
cIMT	Philips CX50 Compact Xtreme system

FFQ developed by the National Institute of Nutrition, Hyderabad.^51^

SES Questionnaire developed by NFHS-2, 1998–1999.^52^

GPAQ developed by WHO.^53^

ACR, albumin-creatinine ratio; cIMT, carotid intimal- media thickness; DXA, dual energy X-ray absorptiometry; FFQ, Food Frequency Questionnaire; GPAQ, Global Physical Activity Questionnaire; HDL, high-density lipoprotein; LDL, low-density lipoprotein; NFHS, National Family Health Survey; SES, socioeconomic status.

Impaired glucose tolerance, impaired fasting glucose and T2DM will be diagnosed based on fasting glucose concentration and glucose concentration 120 min after a 75 g oral glucose load, using WHO criteria.^57^ Hypertension will be defined as systolic pressure >140 mm Hg or diastolic pressure >90 mm Hg or on treatment for hypertension.^58^ We will use International Diabetes Federation criteria for the following outcomes^59^: overweight and obesity: BMI >25 and >30 kg/m^2,^ respectively; central obesity: a waist circumference >90 cm in men and ≥80 cm in women; hypertriglyceridaemia: plasma triglyceride concentration >1.7 mmol/L and low HDL cholesterol:<1.03 mmol/L in men and <1.29 mmol/L in women.

### cIMT measurement

Measurements of cIMT will be made bilaterally using high-resolution B-mode ultrasound with the same machine (Philips CX50 Compact Xtreme) and a 10-MHz linear array probe (Philips) and quantified using the CX50-IMT Philips Quantification application according to American Society for Echocardiography guidelines.^63^ Each common carotid artery will be imaged in three different projections (anterior, lateral and posterior) proximal to the bifurcation. Measurements of IMT will be taken at a plaque-free zone in the far wall of the common carotid artery, captured at the end of diastole. The mean of three readings will be taken. The presence or absence of plaque, defined as a focal structure that encroaches on the arterial lumen by at least 0.5 mm or is more than 50% of the surrounding IMT or has a thickness greater than or equal to 1.5 mm will also be recorded. Between measurer reproducibility in the LV parameters and cIMT will be assessed by the exchange of 10% of scans from each site.

### ECG

All participants will undergo a 12-lead ECG recording. ECGs will be reviewed by a cardiologist, and if there are changes suggestive of ischaemia (ST-depression and/or T wave inversion), detailed Minnesota Coding will be performed. We will use Minnesota codes 1–1 ​and ​​1–2, 4–1 and 4​–2, 5–1 and 5–2 and 7–1 to indicate ischaemic heart disease.^64^

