### Sample size and analysis

We will target the surviving cohort members (1508 from NDBC and 2156 from VBC) who participated in follow-ups between 1998 and 2002. From initial tracing in early 2016, a total of 3500 individuals were recontacted, among whom we expect approximately 1250 in Delhi and 1750 in Vellore to participate (total 3000) in the current protocol.

Exposures in early life will include weight and length at birth: weight, height and BMI and independent conditional weight and height estimates of growth during infancy, childhood and adolescence, as previously described.^48^ Because early growth measurements were measured at different time points and at slightly different ages in both cohorts, and owing to the skewness of BMI, the data will be transformed into SD scores using the lambda-mu-sigma (LMS) method.^66^ The main analysis will use all available data at each time point; it will also be repeated using the subset of participants having data for all time points (birth, infant, childhood and adolescent measurements). Exposures in young adult life will include lifestyle characteristics (diet, physical activity, smoking and alcohol consumption, SES, urban/rural residence and history of rural–urban migration (Vellore only)), anthropometry, lean and fat mass measured by DXA and bioimpedance, metabolic risk markers (plasma glucose, insulin and lipids) and categorical abnormalities as defined above.

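### The trigger for Minnesota coding of ECGs (ST depression or T wave inversion) is narrower than the code list defining ECG ischaemic heart disease, so isolated Q waves have no stated route to coding

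*Protocol article*

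**What the plan says.** The ECG section of the protocol article sets out three steps.

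- Recording covers everyone: "All participants will undergo a 12-lead ECG recording". A cardiologist reviews each tracing.
- Coding is conditional: "if there are changes suggestive of ischaemia (ST-depression and/or T wave inversion), detailed Minnesota Coding will be performed".
- The outcome is defined by codes. The list opens with "We will use Minnesota codes 1–1" and 1-2, continues with 4-1 and 4-2, and closes with "5–1 and 5–2 and 7–1 to indicate ischaemic heart disease".

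The abstract (Methods and analysis) gives the measure outcome status. After the left ventricular measures it lists "carotid intimal-media thickness and ECG indicators of ischaemia".

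The article gives no rule for classifying an ECG that was not sent for coding, and no other section gives Q waves or bundle branch block a separate route to coding.

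**The concern.** The outcome draws on four code families, while the gate in front of coding names two findings. A tracing that shows a counted finding outside those two stops at the gate, so the codes that would make it a case are never assigned. The loss comes from the rule and not from chance. It falls mainly on one kind of case: a Q wave without current ST depression or T wave inversion.

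At stake are the number of ECG-defined cases and what the outcome measures. If uncoded tracings count as negative, the outcome loses cases and its composition shifts towards ST/T change. If they count as missing, whether the outcome is observed depends on the ECG finding itself. The written rule is sound under neither handling.

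**Working it through.** **Trigger against definition.** The article does not spell out what the code numbers stand for. The meanings below are the standard ones of the instrument it names.

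| Codes counted as ischaemic heart disease | Finding | Named in the trigger? |
|---|---|---|
| 1-1, 1-2 | Q/QS waves | No |
| 4-1, 4-2 | ST depression | Yes |
| 5-1, 5-2 | T wave change | Yes (inversion) |
| 7-1 | Left bundle branch block | No |

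- Q wave with ST depression or T wave inversion: sent for coding, and can receive 1-1 or 1-2.
- Q wave alone: not sent for coding, and cannot receive 1-1 or 1-2.
- Left bundle branch block: coded only if the ST/T change that often accompanies it is read as meeting the trigger. That may happen often, but the rule does not ensure it.

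**Is the parenthesis a list of examples?** Elsewhere the article marks examples with an explicit abbreviation, as in the power paragraph for LV mass and in the Discussion for predictors and outcomes. The ECG sentence has no such marker, so it reads as a definition.

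**Figures in the plan.** The article states no prevalence, power or sample size for the ECG outcome, so there is no ECG figure to reproduce. The only binary-outcome power statement concerns LV diastolic dysfunction at 10% prevalence. It serves to check the formula used below:

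Detectable OR per SD = exp[(1.960 + 0.842) / √(n·p·(1−p))]

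- n = 3000, p = 0.10: exp(2.802/√270) = 1.19 (stated 1.19)
- n = 1750: exp(2.802/√157.5) = 1.25 (stated 1.25)
- n = 1250: exp(2.802/√112.5) = 1.30 (stated 1.30)

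**Illustration under assumptions.** Let p be the true prevalence of ECG ischaemic heart disease and q the share of cases showing isolated Q waves. Neither is in the document. With the expected n of 3000 from Sample size and analysis, and uncoded tracings taken as non-cases, missed cases = 3000·p·q and observed prevalence = p(1−q).

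| p (assumed) | True cases | q (assumed) | Missed | Detectable OR, all cases coded | Detectable OR, rule as written |
|---|---|---|---|---|---|
| 2% | 60 | 10% | 6 | 1.44 | 1.47 |
| 2% | 60 | 50% | 30 | 1.44 | 1.67 |
| 5% | 150 | 10% | 15 | 1.26 | 1.28 |
| 5% | 150 | 30% | 45 | 1.26 | 1.32 |
| 5% | 150 | 50% | 75 | 1.26 | 1.39 |
| 10% | 300 | 10% | 30 | 1.19 | 1.20 |
| 10% | 300 | 50% | 150 | 1.19 | 1.26 |

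The proportion of cases lost equals q, which is an input. The table shows what an assumed q would cost in cases and precision. It does not estimate q.

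**Effect on odds ratios.** At p = 5% and q = 30%, 45 missed cases join 2850 true non-cases: 45/2895 = 1.6% of the apparent non-cases. If the isolated-Q-wave share among cases does not vary with exposure, contamination of that size hardly moves the odds ratio for a rare outcome, and the cost is precision.

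**The case against.** **The parenthesis may be shorthand.** A cardiologist sees every tracing, this is a condensed article, and listing 1-1, 1-2 and 7-1 suggests that the authors mean to capture those patterns. The article says that a full protocol can be obtained, and the coding procedure may be set out correctly there. This lowers confidence that tracings are lost in practice. It does not remove the mismatch, because both rules are stated here and they do not fit together. If readers flag Q waves anyway, they depart from the written rule and may do so differently in the two centres.

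**The outcome is peripheral.** None of the four hypotheses mentions ECG or ischaemia, and the power statement does not cover it. This stands, and it limits how much the point matters.

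**Stronger readings a reader might infer.**

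- *Isolated Q waves are definitely analysed as non-cases.* The article does not say so. It is the natural reading, since the outcome is defined only by codes, but it remains an assumption.
- *Associations of ECG ischaemic heart disease with LV mass would be inflated.* The article lists both as outcomes and relates outcomes to early-life, young-adult and current exposures. It plans no regression of one on the other.
- *Sensitivity falls by some stated percentage, such as 10–30%.* Any such figure only returns the assumed share of Q-wave or conduction-only cases.
- *Left bundle branch block is lost in the same way as Q waves.* Secondary ST/T change may often bring it to coding.

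**Conclusion.** The concern holds in limited form: two adjacent sentences in the ECG section conflict. The coding trigger covers two of the four code families that are used "to indicate ischaemic heart disease", and an ECG with isolated Q/QS waves has no stated route to the codes that would make it a case. This is a conflict between stated rules, not a detail left to a fuller document.

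The size cannot be derived from the document. Under assumed prevalences of 2–10% and isolated-Q-wave shares of 10–50%, between 6 (of 60) and 150 (of 300) cases among 3000 participants would go uncoded. At 5% prevalence the detectable OR per SD would rise from 1.26 to between 1.28 and 1.39. These figures rest on assumptions and on treating uncoded tracings as non-cases.

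The supported consequences are under-ascertainment, an outcome weighted towards ST/T change, and lower precision. No bias in a planned association is shown. The point deserves correction because the remedy is cheap, but it does not touch the study's main hypotheses.

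**What to change.** Reconcile the two sentences in one of two ways:

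- widen the trigger to any finding that can yield a counted code: Q/QS waves, ST depression, T wave inversion or left bundle branch block; or
- apply Minnesota coding to all ECGs.

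State in the same place how an uncoded ECG is classified. Apply the same rule to ECGs already reviewed, where the tracings are available, so that both centres and all recruitment periods share one definition. If coding in practice already covers Q waves and bundle branch block, correcting the sentence is enough.

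The cost is a sentence or two of text and some additional tracings to code. With the wider trigger the extra work is limited to tracings with the added findings, and the cardiologist already reviews each one. Coding all ECGs costs more but removes the dependence on a screening judgement.
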